Sutent significantly prolonged time to progression (27 vs. 6 weeks, p<0.001) and improved overall survival (HR 0.49, p=0.007) in a phase III trial of metastatic GIST following failure of imitanib (32). Additionally in two phase II studies, Sutent had an unprecedented 40% objective response rate in cytokine-refractory metastatic renal cell carcinoma (33). Based on these data, Sutent has been approved by the F.D.A. as treatment for GIST whose disease has progressed despite Gleevec or for patients unable to receive Gleevec. Simultaneously, the F.D.A. approved Sutent for treatment of metastatic renal cell carcionoma. In a phase I trial of Sutent in advanced cancers, 50 mg/day was the recommended maximum tolerated dose, with an objective response rate of 21% (34). Sutent is currently undergoing clinical evaluation in multiple tumor types including breast cancer, non-small cell lung cancer, colorectal cancer and prostate cancer. Trials are underway, which will evaluate the efficacy of Sutent in combination with a number of cytotoxic and biological agents including trastuzuzmab, paclitaxel, docetaxel, eroltinib, carboplatin, cisplatin, gemcitabine, irinotecan, oxaliplatin, 5-fluorocuracil, and capecitabine. However, to date, there are no reported clinical studies of Sutent with radiation.

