9.3 Phase I and II Maintenance dose: will be 50 mg PO QD

9.4 Schedule:

- One days 1-28, Sutent will be taken p.o. in the morning
- Two weeks after completion of any chemotherapy, maintenance Sutent in 6 week cycles (consisting of Sutent 50 mg PO QD weeks 1-4 followed by no treatment weeks 5-6) until progression or death

9.5 Formulation and Packaging: SU011248 is a small molecule inhibitor of the receptor tyrosine kinases VEGFR, PDGFR, KIT, and FLT3. In this clinical trial, study medication of SU011248 refers to the investigational agent SU011248 L-malate. Sunitinib L-malate salt will be supplied as hard gelatin capsules containing 12.5-mg, 25-mg, and 50-mg equivalents of Sunitinib malate free base, in bottles containing 30 capsules each."

9.6 Storage:Store at 25º C (*77º F*); excursions permitted to 15-30º C (*59-86º F*).

9.7 Adverse Effects: Data regarding the safety of Sutent are largely from a Phase III randomized trial of 304 patients with metastatic GI stromal tumors following imatinib failure who were treated with Sutent vs. placebo and 169 patients with metastatic renal cell carcinoma treated on phase II trails (32, 33).

Cardiac: Left Ventricular Dysfunction – The incidence of decreased left ventricular ejection fraction to below the lower limit of normal is 11-15% with Sutent vs. 3% for placebo. Over 40% of patients recover left ventricular ejection fraction without intervention. Only 1% of patients suffered grade 3 left ventricular systolic toxicity. Sutent should be discontinued in the presence of clinical congestive heart failure. The Sutent dose should be reduced in all patients without clinical congestive heart failure but with an ejection fraction of <50% and a drop of over 20% from baseline.

Hemorrhagic Events: Bleeding occurred in 18 to 26% of patients receiving Sutent vs. 17% for placebo with epistaxis being the most common hemorrhagic event. The incidence of Grade 3-4 bleeding is 1 to 7% among patients receiving Sutent vs. 9% for placebo. However, fatal pulmonary hemorrhage was noted in two patients with non-small cell lung cancer. Bleeding events, including fatal GI bleeding, has been noted in patients within 30 days of completing Sutent. Although there is no specific contraindication for concurrent anticoagulants, patients requiring continued Coumadin, lovenox, heparin, NSAIDs, aspirin, plavix or similar drugs will be excluded from this study (12/16/09).

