Hypertension: Hypertension was noted in 15 to 28% of patients receiving Sutent vs. 11% for placebo. Grade 3 hypertension occurred in 4 to 6% of patients receiving Sutent vs. 0% for placebo. No case of grade 4 hypertension was reported. Careful monitoring and use of antihypertensive therapy is recommended. Sutent should be discontinued in cases of severe hypertension (defined as >200 mgHg systolic or >110 mgHg diastolic).

Adrenal: Adrenal toxicity was noted in rats and monkeys treated with Sutent but to date, there have been no cases of clinical adrenal insufficiency, adrenal necrosis or hemorrhage in human clinical trials. Nonetheless, patients receiving Sutent that experience stress such as surgery, trauma or severe infection should be monitored for adrenal insufficiency.

Gastrointestinal: Diarrhea, nausea, stomatitis, dyspepsia and vomiting were the most commonly reported gastrointestinal events occurring in patients who received Sutent. Diarrhea and stomatitis occurred more commonly in patients treated with Sutent than placebo. Supportive care for gastrointestinal adverse events, such as anti-nausea or anti-diarrheal medication should be prescribed as needed.

Skin: Skin discoloration, often to a yellowish hue occurred in approximately 1/3 of patients treated with Sutent. Depigmentation of the hair or skin, dryness, cracking, blistering or rash was also reported.

9.8 Potential Drug-Drug Interactions: SU11248 is mediated metabolized by the liver by CYP3A4. Therefore CYP3A4 inducers such as rifampin will result in a 56-79% reduction in SU11248 serum doses while CYP3A4 inhibitors such as ketoconazole will result in a 59-76% increase in SU11248 serum doses. For patients who are being concomitantly treated with a potent CYP3A4 inhibitor or CYP3A4 inducer, alternative treatments that lack potent CYP3A4-inducing properties should be considered. For patients who require treatment with a potent CYP3A4 inhibitor, a dose reduction should be considered in the presence of severe adverse events. For patients who require treatment with a potent CYP3A4 inducer, a dose increase should be considered.

However, in-vitro studies indicate that SU11248 does not induce or inhibit the major CYP450 enzymes including CYP3A4.

9.9 Administration: Sutent may be taken with or without food. The following schedule is recommended for the phase I and phase II studies:

| **REGISTER** | *Treatment* | *Days*  *1-7* | *8-12* | *13-14* | *15-19* | *20-28* | *29-42* |

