9.10 Dose Modifications for Sutent(Applies only to phase II)

Dose modification of Sutent can be secondary to any grade 3 toxicity related to Sutent according to the judgment of the treating physician. When toxicities eliciting dose modification occur, Sutent will be temporarily discontinued but restarted at the next lower dose level when the toxicity has resolved to grade 2 or lower. In the event of hospitalization for reasons other than drug toxicity, patients should be directed to continue trial drug at the discretion of their physician. The principal investigator should be notified immediately of any compliance issues that arise in the course of the trial. If a patient still experiences dose-modifying toxicities despite drug holiday and reduced dose schedule, the patient, if benefiting from treatment, should stop receiving Sutent and continue radiation.

The following toxicities, in addition to any other toxicity as judged by the treating physician, merit temporary discontinuation should be considered dose-limiting toxicity:

1. Any CTC grade 3 or 4 non-hematopoietic adverse event that the investigator considers consistent with a drug-related toxicity;

2. Any CTC grade 4 hematopoietic adverse event that the investigator considers consistent with a drug-related toxicity;

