#### a) Phase I Trials

#### Investigators will conduct continuous review of data and patient safety at their biweekly Clinical Trials Quality Assuarance meetings where the results of each patient’s treatment are discussed and the discussion is documented in the minutes. The discussion will include for each dose level: the number of patients, significant toxicities as described in the protocol, dose adjustments, and responses observed. Quarterly summaries will be submitted to the Clinical Trials Monitoring Committee for review.

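### Section 9.8 permits potent CYP3A4 drugs and an uncapped Sutent increase with inducers, so a phase I patient can be counted at a Sutent dose or exposure other than the one assigned

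*Protocol*

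**What the plan says.** Section 9.8 states that inducers such as rifampin cause "a 56-79% reduction in SU11248 serum doses while CYP3A4 inhibitors such as ketoconazole will result in a 59-76% increase in SU11248 serum doses". For patients on either class it says "alternative treatments that lack potent CYP3A4-inducing properties should be considered". The sentence opens with both inhibitors and inducers, but the alternatives it names are only those that do not induce; this looks like a drafting slip.

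For a patient who cannot do without an inhibitor, a dose reduction is considered once severe adverse events appear. For a patient who cannot do without an inducer: "For patients who require treatment with a potent CYP3A4 inducer, a dose increase should be considered". Neither the size of the increase, nor a ceiling, nor the phase of the study is given.

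Sections 4 and 5 and the eligibility checklist do not mention CYP3A4 drugs. Sections 9.1 and 10 set phase I Sutent at 25 mg (level 1), 37.5 mg (levels 2 and 3) and 50 mg (levels 4 and 5). Section 10 escalates after 0 DLTs in 3 patients or fewer than 2 in 6, counting every treated patient at the assigned level.

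**The concern.** Advice to consider a dose change may suit a drug given at a settled dose. In phase I of this study the Sutent dose is one of the two quantities under test, and very few patients decide each level. A drug that moves exposure by more than one planned step means the patient does not inform the level to which he or she is credited.

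With an inducer there are two alternative outcomes:

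- If Sutent is not raised, the patient is under-exposed and can help clear the level.
- If Sutent is raised, the patient takes a dose that is not the assigned one.

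With an inhibitor, exposure is above the assigned level, and a resulting DLT can help stop escalation.

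The MTD and the phase II dose follow from these counts. Only the Sutent part of each level is affected; the moves from level 2 to 3 and from 4 to 5 change radiation alone.

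**Working it through.** **Inputs.** Sutent doses are from Sections 9.1 and 10. Exposure changes are from Section 9.8. Capsule strengths are from Section 9.5: "hard gelatin capsules containing 12.5-mg, 25-mg, and 50-mg equivalents of Sunitinib malate free base". The plan gives no figure of its own on this point to reproduce.

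**Planned Sutent steps.** Upward: 37.5/25 - 1 = +50% and 50/37.5 - 1 = +33%. Downward: 25/37.5 - 1 = -33% and 37.5/50 - 1 = -25%. The smallest inhibitor effect (+59%) exceeds both upward steps, and the smallest inducer effect (-56%) exceeds both downward steps.

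**Dose-equivalent exposure.** This assumes that exposure is proportional to dose and that the serum figures in 9.8 describe exposure. The inhibitor multiplier is 1.59 to 1.76. The inducer multiplier is 1 - 0.79 = 0.21 to 1 - 0.56 = 0.44. The smallest raise the capsules allow is 12.5 mg.

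| Assigned (mg) | With inhibitor | With inducer | Dose after smallest raise | Exposure after raise, with inducer |
|---|---|---|---|---|
| 25 | 39.8-44.0 | 5.3-11.0 | 37.5 | 7.9-16.5 |
| 37.5 | 59.6-66.0 | 7.9-16.5 | 50 | 10.5-22.0 |
| 50 | 79.5-88.0 | 10.5-22.0 | 62.5 | 13.1-27.5 |

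Every unadjusted inducer value lies below the 25 mg of level 1. After the smallest raise, neither the dose nor the exposure matches the assigned level. Full offset, which 9.8 does not ask for, would take 1/0.44 = 2.3 to 1/0.21 = 4.8 times the dose.

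**Effect on one 3+3 decision (illustration; all DLT risks are assumed).** One first-cohort patient has DLT risk q and all others have risk p:

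- P0 = (1-q)(1-p)²
- P1 = q(1-p)² + 2p(1-p)(1-q)
- P(escalate) = P0 + P1(1-p)³

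At p = 0.4 with nobody affected: 0.216 + 0.432 × 0.216 = 0.309. With an uncompensated inducer patient at q = 0.3, 0.2 or 0.1 the result is 0.348, 0.386 or 0.425.

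At p = 0.2 with nobody affected: 0.512 + 0.384 × 0.512 = 0.709. With an inhibitor patient at q = 0.3, 0.4 or 0.5 the result is 0.661, 0.613 or 0.566.

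The shifts are therefore about 4 to 12 points upward (inducer) and 5 to 14 points downward (inhibitor), given that one first-cohort patient is affected.

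**Allowing for rarity.** If 5% of patients were affected (assumed), the chance of at least one in three is 1 - 0.95³ = 14%. The shifts then average roughly 0.6-1.7 points (inducer) or 0.7-2.0 points (inhibitor). At 1% the chance is 1 - 0.99³ = 3%, and the averages are about 0.1-0.4 points.

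**The case against.** **Phase I doses are fixed anyway.** Sections 9.1, 9.9 and 10 set the dose by level, and the section on Sutent dose modification (9.10) is headed as applying to phase II only. On this view 9.8 is background drug information. That reading is reasonable but not secured. Section 9.10 concerns toxicity: "Dose modification of Sutent can be secondary to any grade 3 toxicity related to Sutent". Section 9.8 carries no phase limit. Section 9.7 orders a cardiac reduction without one: "The Sutent dose should be reduced in all patients without clinical congestive heart failure" who meet its ejection-fraction criteria. Appendix 3 expects review of phase I trials to cover "significant toxicities as described in the protocol, dose adjustments, and responses observed". And even if the assigned dose always holds, the altered exposure remains.

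**It will be rare and visible.** Both drugs named in 9.8 are anti-infectives. Section 5 (items 2 and 6) excludes active infection, and the checklist asks about infection requiring antibiotics. Medications are recorded (Sections 7.1, 7.2 and 7.4), and cases are reviewed every two weeks. This stands as a limit on frequency. It does not bar the drug classes, and seeing a changed dose does not restore the assigned one.

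**Counting rules may sit in a statistical analysis plan.** This largely stands. Who is evaluable for DLT is commonly settled there, so a missing counting rule in Section 10 is not the main fault. What the protocol itself fixes badly is eligibility, permitted drugs and the dose instruction. Section 11.1 does not fill the gap: its rule on non-protocol toxicity is written for chemotherapy, surgery and radiation.

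**A reader might infer an overdose hazard.** Section 2c reports that "50 mg/day was the recommended maximum tolerated dose" for Sutent alone, and a raise at levels 4 and 5 goes nominally above it. The figures do not support that inference. At 62.5 mg with an inducer, exposure is only about 13-27.5 mg equivalent, and passing the assigned exposure would take at least a 2.3-fold raise.

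**Conclusion.** The point holds and is worth an amendment. Section 9.8 lets patients who require potent CYP3A4 drugs take part, and for inducers it invites a Sutent increase with no size, cap or phase limit. By its own figures these drugs shift exposure by more than one planned Sutent step, in either direction and at every level. Section 10 would then count the patient at a dose or exposure other than the one assigned.

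The comparison of percentages is plain arithmetic on the protocol's figures. The milligram equivalents assume dose-proportional exposure and extend figures given for two example drugs to whole classes. The 3+3 probabilities are illustrations on assumed DLT risks. The frequency is not stated and is probably low, so confidence in the practical effect is moderate. The documents do not show that the MTD will be wrong, only that the rules as written allow a level to be cleared or stopped on the wrong Sutent dose or exposure. The 9.8 reduction for inhibitor users with severe adverse events is not at issue.

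**What to change.** For phase I:

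1. Add to Section 5 an exclusion for required use of potent CYP3A4 inhibitors or inducers. It should run from day 1 until the later of two dates: the end of concurrent Sutent (day 28, or day 42 under the variant for 3 to 5 sites in Section 8.1) and the end of DLT observation. Section 16 puts the latter at about day 8 + 30 = day 38. Section 10 requires at least 30 days of follow-up after patients have been treated, which may end later, so a fixed day 38 would be too early for some patients.
2. State in 9.8 that its inducer dose increase does not apply in phase I during that period. Correct the sentence on alternatives so that it covers drugs lacking potent CYP3A4 inhibition as well as induction.

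Optionally, add to Section 10 that a patient who must start a potent inducer in that period and has no DLT is replaced, while any DLT counts. This leans cautious. The slot's DLT risk becomes q + (1-q)p. At p = 0.4 and q = 0.3, 0.2 or 0.1 that is 0.58, 0.52 or 0.46, and escalation is 24%, 26% or 29% instead of 31%. At p = 0.2 and q = 0.1 it is 0.28, and escalation is 67% instead of 71%. Inhibitors need no separate counting rule.

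The cost is a short amendment and an occasional phase I exclusion or replacement. Section 5, item 10, already excludes patients who must continue anticoagulants, although Section 9.7 notes no specific contraindication, so the approach has a precedent in this protocol. Medications are already recorded.

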**Sutent will be taken by mouth every morning on days 1-28**

**Phase I Dose Levels**

| **Dose Level** | **Radiation Dose** | **Sutent Dose** |
| --- | --- | --- |
| 1 | 40 Gy in 10 fractions | 25 mg PO QD |
| 2 | 40 Gy in 10 fractions | 37.5 mg PO QD |
| 3 | 50 Gy in 10 fractions | 37.5 mg PO QD |
| 4 | 50 Gy in 10 fractions | 50 mg PO QD |
| 5 | 60 Gy in 10 fractions | 50 mg PO QD |

**Phase II dose level will be MTD determined by Phase I**

**↓**

Additional chemotherapy (as determined by Medical Oncology)

**↓**

Maintenance Sutent (until death or progression) and appropriate follow-up

- Two weeks after completion of any chemotherapy, maintenance Sutent in 6 week cycles (consisting of Sutent 50 mg PO QD weeks 1-4 followed by no treatment weeks 5-6) until progression or death

9.10 Dose Modifications for Sutent(Applies only to phase II)

Dose modification of Sutent can be secondary to any grade 3 toxicity related to Sutent according to the judgment of the treating physician. When toxicities eliciting dose modification occur, Sutent will be temporarily discontinued but restarted at the next lower dose level when the toxicity has resolved to grade 2 or lower. In the event of hospitalization for reasons other than drug toxicity, patients should be directed to continue trial drug at the discretion of their physician. The principal investigator should be notified immediately of any compliance issues that arise in the course of the trial. If a patient still experiences dose-modifying toxicities despite drug holiday and reduced dose schedule, the patient, if benefiting from treatment, should stop receiving Sutent and continue radiation.

The following toxicities, in addition to any other toxicity as judged by the treating physician, merit temporary discontinuation should be considered dose-limiting toxicity:

1. Any CTC grade 3 or 4 non-hematopoietic adverse event that the investigator considers consistent with a drug-related toxicity;

2. Any CTC grade 4 hematopoietic adverse event that the investigator considers consistent with a drug-related toxicity;

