**Treatment Plan**:

- Sutent be administered PO QD from days 1 to 28 (see Figure 1)

Figure 1. Treatment Schema

Determine eligibility

**↓**

| **REGISTER** | **Treatment** | Days  1-7 | 8-12 | 13-14 | 15-19 | 20-28 | 29-42 |
| --- | --- | --- | --- | --- | --- | --- | --- |
| XRT |  | X |  | X |  |  |
| Sutent | X | X | X | X | X |  |

**↓**

Additional chemotherapy (as determined by Medical Oncology)

**↓**

Maintenance Sutent (until death or progression) and appropriate follow-up

- Radiation therapy will start on day 8 and will be given to each site for ten fractions
- Fractions must be separated by at least 16 hours
- The MTD of radiation in combination with Sutent will be determined
- Doses of radiation and Sutent will increase as shown in Table 1 in order to determine the MTD of radiation in Gy and Sutent in mg
- The RPTD will be one dose level lower than the MTD. If the MTD is not reached at dose level 5, no further escalation will occur and this will be the RPTD. The RPTD will then be used for future phase II trials.
- Starting day 43, chemotherapy may be given, as determined by the treating medical oncologist.
- Two weeks after completion of any chemotherapy, maintenance Sutent in 6 week cycles (consisting of Sutent 50 mg PO QD weeks 1-4 followed by no treatment weeks 5-6) until progression or death
- If no chemotherapy is planned, maintenance Sutent (as described above) will start on day 43.

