**Phase I Dose Levels**

| **Dose Level** | **Radiation Dose** | **Sutent Dose** |
| --- | --- | --- |
| 1 | 40 Gy in 10 fractions | 25 mg PO QD |
| 2 | 40 Gy in 10 fractions | 37.5 mg PO QD |
| 3 | 50 Gy in 10 fractions | 37.5 mg PO QD |
| 4 | 50 Gy in 10 fractions | 50 mg PO QD |
| 5 | 60 Gy in 10 fractions | 50 mg PO QD |

1. Radiation Doses (Phase II): The radiation dose used in the MTD dose level will be used throughout the phase II portion of this study.
2. Dose/volume constraints: The dose distribution will be converted to the normalized isoeffective dose, equivalent to dose given at standard fractionation (2 Gy per fraction). Normal tissue tolerance doses to be used as guidelines for treatment plan evaluation are: (based on the treatment on the sum of all involved sites):
3. Spinal cord:
   - 1. Must keep each dose < 300 cGy/fraction (therefore maximum total spinal cord dose will be 3000 cGy)
     2. Same segment of spinal cord must not be in more than 1 treatment field
   1. Skin: Maximum skin dose 40 Gy
   2. Lung: Volume receiving > 20 Gy less than 30%
   3. Liver: Volume receiving > 30 Gy less than 50%
   4. Kidney: Volume receiving > 20 Gy (both kidneys) should be less than 50%
   5. Esophagus: Maximum esophageal dose ≤ 40 Gy
   6. Heart: Volume >25 Gy less than 60% and maximum heart dose <30 Gy
   7. Major Vessels: Maximum dose 40 Gy
   8. Bone marrow: Must limit the radiation to < 30% of bone marrow

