**9. DRUG THERAPY - SUTENT**

9.1 Phase I Dose (days 1-28):

| **Dose Level** | **Radiation Dose** | **Sutent Dose** |
| --- | --- | --- |
| 1 | 40 Gy in 10 fractions | 25 mg PO QD |
| 2 | 40 Gy in 10 fractions | 37.5 mg PO QD |
| 3 | 50 Gy in 10 fractions | 37.5 mg PO QD |
| 4 | 50 Gy in 10 fractions | 50 mg PO QD |
| 5 | 60 Gy in 10 fractions | 50 mg PO QD |

9.2 Phase II Dose (days 1-28): Phase II will be the MTD from Phase I

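### The Sutent restart rule in 9.10 steps down paired dose levels, so read literally it leaves the drug dose unchanged from levels 5 and 3, and it gives phase I maintenance no step

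*Protocol*

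**What the plan says.** **Restart rule.** Protocol 9.10 lets the treating physician modify Sutent for related grade 3 toxicity, and then fixes the restart: "Sutent will be temporarily discontinued but restarted at the next lower dose level when the toxicity has resolved to grade 2 or lower". The following step begins "If a patient still experiences dose-modifying toxicities despite drug holiday and reduced dose schedule" and ends in stopping Sutent. The section is headed "9.10 Dose Modifications for Sutent(Applies only to phase II".

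**Dose levels.** The table in 9.1, repeated elsewhere in the protocol, defines five levels, each a radiation dose joined to a Sutent dose. Level 4 is "50 Gy in 10 fractions | 50 mg PO QD" and level 5 is "60 Gy in 10 fractions | 50 mg PO QD". There is no separate list of Sutent steps.

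**Phase II regimen.** Section 8.1 holds radiation constant: "The radiation dose used in the MTD dose level will be used throughout the phase II portion of this study". The synopsis (Treatment Plan) makes level 5 a planned phase II dose: "If the MTD is not reached at dose level 5, no further escalation will occur and this will be the RPTD".

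**Maintenance.** 9.3 sets 50 mg daily for both phases, and 9.4 continues it in six-week cycles until the patient progresses or dies.

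**Other reductions.** 9.7 (Cardiac) wants the Sutent dose "reduced in all patients without clinical congestive heart failure but with an ejection fraction of <50% and a drop of over 20% from baseline". 9.8 asks that a reduction be considered for patients on a potent CYP3A4 inhibitor who have severe adverse events. Neither is limited to a phase, and neither says by how much.

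**The concern.** A restart rule after grade 3 drug toxicity should lead every reader to the same lower dose. This one points to a ladder in which radiation and drug rise in turn, so one rung down does not always lower the drug. Followed as written, it can return a patient to the Sutent dose that caused the toxicity.

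The phase II limit leaves a second gap. Phase I patients also take 50 mg maintenance, including those who had only 25 or 37.5 mg in the concurrent course, yet 9.10 does not reach them. What is at stake is consistent and safe dosing.

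**Working it through.** No figure of the plan needs reproducing. The check is to look up the Sutent dose at each level and one level down (table in 9.1), and then compare the scope of each reduction rule.

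**Step 1: one level down, read literally.** Change = Sutent at level k−1 minus Sutent at level k.

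| From level | Sutent now (mg) | Sutent one level down (mg) | Change |
| --- | --- | --- | --- |
| 5 | 50 | 50 | 0 |
| 4 | 50 | 37.5 | −12.5 mg (−12.5/50 = −25%) |
| 3 | 37.5 | 37.5 | 0 |
| 2 | 37.5 | 25 | −12.5 mg (−12.5/37.5 = −33%) |
| 1 | 25 | none | undefined |

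Two of the four defined steps change only the radiation dose (60 to 50 Gy from level 5, 50 to 40 Gy from level 3). Section 8.1 fixes radiation in phase II, so from those levels the patient resumes the same regimen. Level 1 is a different gap: no level lies below it.

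**Step 2: consistency within 9.10.** The next step in 9.10 presumes that a reduced dose has been given. From level 5 or 3 the literal rule supplies none, so the literal reading conflicts with the section's own next sentence.

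**Step 3: the same lookup on Sutent alone.** With the ladder 50, 37.5, 25 mg, levels 5 and 4 go to 37.5 mg, levels 3 and 2 go to 25 mg, and 50 mg maintenance goes to 37.5 mg. Every restart from 50 or 37.5 mg is then a true reduction. Only the action below 25 mg remains to be written.

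**Step 4: maintenance.** 50 mg is not a numbered level; it is the Sutent dose of both level 4 and level 5. One level down is 37.5 mg if it is matched to level 4 and 50 mg if matched to level 5. Over a 28-day treatment period that is 50 × 28 = 1400 mg against 37.5 × 28 = 1050 mg, a difference of 350 mg (25%).

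**Step 5: what phase I maintenance has in writing.** Section 6 allows discontinuation for adverse events. 9.7 gives stopping rules for clinical heart failure and severe hypertension. The ejection-fraction rule in 9.7 and the CYP3A4-inhibitor rule in 9.8 call for or allow a reduction of unstated size. For any other grade 3 Sutent toxicity there is no reduction step.

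**Step 6: timing against DLT assessment.** This decides how the scope of 9.10 can be widened. Section 16 counts DLTs for 30 days from the start of radiation: 8 + 30 = day 38. Section 10 follows patients for at least 30 days after they have been treated: 19 + 30 = day 49 from the last radiation day, or 28 + 30 = day 58 from the last concurrent Sutent day. Maintenance can start on day 43. Section 8.1 also lets some patients with 3 to 5 sites take concurrent Sutent to day 42. A scope defined by the end of DLT assessment would therefore be unclear; one defined by maintenance is not.

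**The case against.** The strongest reply is that 9.10 excludes the literal reading. The section concerns Sutent, the sentence is about Sutent, phase II radiation cannot move, and the next sentence assumes a lower dose. A clinician would probably go from 50 to 37.5 to 25 mg. This stands as to intent. A reader might infer that patients will in practice be restarted at the toxic dose; the documents do not support that. They do leave the intended step unwritten, in a sentence stated as a rule. Physician judgment in 9.10 governs whether to modify, not the restart dose.

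The maintenance ambiguity largely follows from the same wording: on a Sutent-only ladder 50 mg has one next dose. 9.10 also ends by telling the patient to carry on with radiation, which fits the concurrent course, so it is not certain that the section was written for maintenance. If it was not, maintenance has no general step in either phase.

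A reader might also infer that phase I maintenance offers only full dose or stopping. That is not so: 9.7 and 9.8 both provide for reduction, without a phase limit. What is missing is the amount, and any step for other grade 3 toxicity.

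Finally, keeping reductions out of the phase I concurrent course is defensible, because they would blur the dose under test. That reason does not extend to maintenance, where everyone gets 50 mg whatever the level under test.

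**Conclusion.** The point holds as a wording defect in a dosing rule, of minor severity. Read literally, 9.10 gives no Sutent reduction from levels 5 and 3 and is undefined at level 1. Its phase II limit leaves phase I maintenance without a general reduction step.

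The size is 12.5 mg a day between the two readings from 50 or 37.5 mg. Phase II uses a single level, so in its concurrent course the problem arises only if that level is 5, 3 or 1. Level 5 is the planned choice if the MTD is not reached. The protocol gives no rate of dose reduction, so the number of patients affected is unknown.

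The conclusion assumes that a dose level means a numbered row of the table, the only definition given. A reader might extend it to bias in the MTD, lost power or a distorted progression-free survival; nothing in the documents supports that, and it is not claimed.

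**What to change.** 1. In 9.10, replace the reference to the level below with: *the next lower Sutent dose (50 to 37.5 to 25 mg), radiation dose unchanged*. The investigators should write in the action below 25 mg, either stopping or 12.5 mg.
2. Change the scope in the 9.10 heading to: *Applies to phase II, and to maintenance Sutent in phase I*. The phase I concurrent course stays outside it, including the section 8.1 variant that runs to day 42.
3. Add that toxicity already counted as a DLT under sections 10 and 16 stays counted whether or not the maintenance dose is later reduced.
4. In 9.7 (ejection fraction) and 9.8 (potent CYP3A4 inhibitors), refer to the 9.10 step for the size of the reduction, leaving the criteria as they are.

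The cost is a short dosing amendment that the investigators must approve. No visit, test or patient is added. The capsules in 9.5 already make every step: 25 + 12.5 = 37.5 mg, 25 mg, and 12.5 mg if wanted.
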